### Sample size

The study is designed to detect a significant difference in the pre- and post-intervention time points for a given dichotomous variable [42, 43].$$\mathrm N=\left\{{\mathrm p}_1\;\left(100-{\mathrm p}_1\right)+{\mathrm p}_2\;\left(100-{\mathrm p}_2\right)\right\}\times{\mathrm f}_{\left(\mathrm\alpha,\mathrm\beta\right)}/\left({\mathrm p}_1-{\mathrm p}_2\right)^2$$

Where;$$\mathrm{N}=\text{Minimum sample size required for each group}$$$$\begin{aligned} \alpha=\:&\text{The level of significance used for detecting} \\& \text{an intervention difference}\:(0.05) \end{aligned}$$$$\begin{aligned} 1- \beta=\:&\text{The degree of certainty (power) that the difference p1-p2}, \\&\text{if present would be detected, often set at 0.8 (0.2)} \end{aligned}$$

$$f=\text{A function of}\ \alpha\ \mathrm{and}\ \beta\ \mathrm{when}\ \alpha\ \text{is 0.05 and}\ \beta\ \text{is 0.02 (7.9)}$$
$$\begin{aligned} \mathrm{P}_1=\:&\text{Expected percentage of an outcome variable}\\& \text{at the baseline of the intervention} \end{aligned}$$
$$\begin{aligned} \mathrm{P}_2=\:&\text{Expected percentage of an outcome variable} \\&\text{at the end of intervention} \end{aligned}$$

Previous interventional studies on fermented food have shown that host nutritional status, health and immune parameters are predominantly affected by the change in host gut microbiome [42–45]. Therefore, change of gut microbiome composition was used for sample size calculation. Previous studies have used the percentage presence of selected taxonomic groups of microbiota to interpret the gut microbiome changes [7, 46, 47]. Therefore, P1 and P2 in this study were derived based on a 17-week randomized controlled intervention study (*n* = 18, healthy adults) on high fiber food-based diet where percentage presence of *Oscillospira* at baseline was 31% and at the end of the intervention was 73% [7].

Therefore;

P_1_ = Expected percentage presence of Oscillospira at T_1_ = 31% [7] P_2_ = Expected percentage presence of Oscillospira at T_2_ = 73% [7]

The sample size obtained (*n* = 18.41) was corrected to account for design effect due to clustering (d). In most interventional studies, the maximum d has been reported as 2, and therefore the design effect was considered as 2 for this trial [48, 49]. Therefore, after correction, the sample size was 36.82. With another 25% non-response added, the final sample size was 45 participants.

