## Background

Sri Lanka, a county in South Asia, has a wide variety of traditional rice and rice-based meals that link people with their rich culinary culture. This culture promotes sustainable food consumption practices, including a variety of unique preservation methods for maximum food utilization. *Diyabath* is one such traditional Sri Lankan pre-breakfast meal prepared by fermenting leftover cooked rice (from dinner) overnight, contributing to reduced food wastage. Diverse communities in Sri Lanka enhance the gastronomic value of *diyabath* by adding different ingredients such as chilies, onions and coconut milk at different stages of fermentation. This flavour infusion is a practice that not only improves the sensory quality but also adds nutritional and medicinal value. Therefore, there are different recipes of *diyabath* consumed by Sri Lankans since many decades. *Diyabath* is also used by Sri Lankan indigenous medical practitioners as a dietary remedy for conditions like gastritis and anaemia [1, 2].

In recent years, the consumption of fermented foods containing live microorganisms has emerged as an important dietary strategy for improving human health [3]. Fermentation of cereals and grains is shown to reduce the phytate activity leading to better absorption of vital minerals such as iron and zinc in the gut, and thereby enhance the bioavailability of protein [3, 4]. Further, it could produce certain desirable micronutrients such as vitamin B_12_ [5, 6]. In terms of health benefits, studies have shown positive outcomes upon consumption of fermented food in apparently healthy adults. A randomized interventional study reported enhancement of the gut health and immune parameters following a 17-week high-fermented-food diet [7], while another showed enhanced glucose metabolism following the consumption of sourdough bread (an Egyptian fermented food) [8].

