**Fig. 3 Fig3:**
[figure not shown]
Time structure of the trial

Primary outcomes of the study include changes in the following parameters:*Host gut microbiome composition:* Evaluated using percentage abundance of probiotic strains (i.e. *Lactobacillus* spp, *Bifidobacterium* spp) and other beneficial microorganisms (i.e. *Oscilllospira*, *Akkermansia muciniphila*), alpha-diversity index and firmicutes-to-bacteroidetes ratio (F/B). Diversity index reveals the change in the gut microbiome composition and is important to have a balanced ratio between the most common two phyla (Firmicutes and Bacteroidetes F/B) for homeostasis of the gut [38]. Gut microbiota is directly responsible to develop digestive, immunological and metabolic functions in host [39, 40].*Nutritional status and health parameters*: Evaluated by serum micronutrients and serum ferritin*Health biomarkers*: Assessed by lipid profile, high-sensitivity C-reactive protein (hsCRP), fasting blood sugar (FBS), aspartate aminotransferase (AST), alanine aminotransferase (ALT) and serum insulin*Immune markers:* Evaluated by analysing interleukin-6 (IL-6), IL-10 and cytokines

Each participant is expected to improve these parameters to either reach a healthy limit or a healthier end if already in the healthy limit.

Secondary outcomes of the study include:*Antioxidant capacity:* An increase in total antioxidant capacity in serum after consumption of an antioxidant rich food indicates absorption of antioxidants from the food and an enhanced in vivo defence status against oxidative stress [41].*Anthropometry:* Measured as waist circumference, hip circumference and BMI

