### Recruitment

The study setting has on average 80 women hostellers. The principle investigator (PI) will approach them through hostel authorities and will conduct an introductory session on the intervention procedure, potential risks and benefits of the study. Those who express interest will be given an information sheet in local languages (Sinhala and Tamil), with sufficient time to review the information and opportunities to ask questions and seek clarification from the investigation team. Using the hostel registry, potential candidates will then be identified using simple random sampling and screened for their eligibility for the study. This screening will include a clinical assessment including BMI performed by a medical officer who is not involved in the study. Relevant documents will be reviewed to confirm certain exclusion criteria. In addition, an interviewer-administered food frequency questionnaire (FFQ) validated for Sri Lankan adults will be administered to get a clear understanding of the participant’s usual dietary pattern [50]. Those already consuming *diyabath* or any other rice-based fermented food will be excluded from the study. Once eligibility is established based on the screening results, the potential candidates will be invited to participate in the study and informed written consent obtained by the PI.

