### Statistical analysis

Data will be analysed using the statistical package for the for the Social Sciences (SPSS) version 21.0. The changes in nutritional, health and immune parameters between the baseline (T_0_) and at the end of control phase (T_1_) will be analysed first to identify any significant change with time. The end point of control phase will serve as the pre-intervention point for further assessments. The changes in outcomes between the pre-intervention point (T_1_) and at the end of intervention phase (T_2_) will be analysed to determine any significant effects of *diyabath* consumption on the study group.

Paired t-test will be performed to determine the significance of the mean difference of pre- and post- measurements during the intervention phase. *P* value less than 0.05 is considered statistically significant.$$\begin{aligned} {\mathrm H}_0=\:&\left[\mathrm{Pre}-\mathrm{intervention}\;\mathrm{measurements} -\mathrm{post}\right. \left.-\:\mathrm{intervention}\;\mathrm{measurements}\right]=0 \end{aligned}$$

The same analysis will be performed in relation to the control phase. This evaluation is important to reveal any possible change in parameters that can occur due to seasonal, physiological or climatic changes in individuals.

Further, independent sample t-test will be performed to assess the significance between the intervention and control phases, in relation to the mean change in pre- and post-measurements observed during the intervention and control phases.$$\begin{aligned} {\mathrm H}_0=\:&\left[\mathrm{Mean}\;\mathrm{change}\;\mathrm{in}\;\mathrm{control}\;\mathrm{phase} \right. \left. -\:\mathrm{Mean}\;\mathrm{change}\;\mathrm{in}\;\mathrm{intervention}\;\mathrm{phase}\right]=0 \end{aligned}$$

Bioinformatics analysis of metagenomics of microorganisms evaluated from stool samples will be carried out based on16S amplicon sequence variants (ASVs) model.

Analysis of the effect of diyabath on primary outcomes will be based on modified intention-to-treat (mITT) and per-protocol (PP) principles. The mITT population will include participants who completed the first 15 weeks of the study period which covers the control phase and half of the intervention phase. The PP population will include the participants who completely adhered to the study protocol [53]. Missing data will be adjusted with multiple imputation.

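### The sample size is worked out for an unpaired presence/absence comparison with a clustering correction, so its 80% power belongs to none of the t-tests the protocol names

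*Protocol article*

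**What the plan says.** The Sample size section sets out its aim as follows: "The study is designed to detect a significant difference in the pre- and post-intervention time points for a given dichotomous variable". Its formula has the variance terms of two separate proportions, and N is defined as "Minimum sample size required for each group". The inputs are the percentage of people in whom Oscillospira is present, 31% before and 73% after, taken from an 18-person study. The result, 18.41, is doubled because "the design effect was considered as 2 for this trial", giving 36.82. A 25% non-response allowance leads to 45.

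Other sections describe something different. Study design and Implementation give a single arm in which the same women supply both control and intervention data. Study setting names one women's hostel. Recruitment says "The study setting has on average 80 women hostellers" and selects candidates from its registry by simple random sampling. Under Outcomes the microbiome is "Evaluated using percentage abundance of probiotic strains" and other beneficial organisms, plus alpha-diversity and the Firmicutes/Bacteroidetes ratio. Under Statistical analysis, "Paired t-test will be performed to determine the significance of the mean difference of pre- and post- measurements during the intervention phase"; the same test is applied to the control phase, and an independent-sample t-test compares the two phases' mean changes. No test of proportions, paired or unpaired, is named.

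**The concern.** Three things do not fit together.

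- **Pairing.** The formula has no term for within-woman correlation or discordant pairs, although every comparison is within women.
- **Endpoint and test.** N is calculated for presence or absence, while the listed outcomes are continuous and the named tests compare means.
- **Clustering.** A design effect inflates variance when whole clusters are sampled or compared. Here there is one hostel, women are sampled individually, no clusters are compared, and no named analysis handles clustering. Yet the doubling supplies half of the pre-dropout N.

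At stake is what the power statement tells a reader. The protocol gives no mean change or SD for any primary outcome. One therefore cannot tell what change in abundance, ferritin or IL-6 the trial can detect, or how much larger an effect the between-phase comparison needs. That comparison is the one that addresses change over time.

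**Working it through.** **1. Reproduce the plan's figure.** Inputs from Sample size: P1 = 31, P2 = 73, f = 7.9.

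N = (31×69 + 73×27) × 7.9 / 42² = (2139 + 1971) × 7.9 / 1764 = 18.41.

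Doubled: 36.82. Times 1.25: 46.0 (45 is stated). 45 less 25% leaves 33.75, taken as 34 evaluable.

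The value f = 7.9 fits two-sided alpha 0.05 and beta 0.2: (1.960 + 0.842)² = 7.85. The section prints beta as 0.02 beside it, which would need f = 16.1. The same section sets power at 0.8, so 0.02 is a misprint.

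**2. Power of the sized test at the final N.** Unpaired proportions without a design effect: power = Φ(0.42 / √[(0.31×0.69 + 0.73×0.27)/n] − 1.96). This gives 80% at n = 18.41, 97% at 33.75 and 99% at 45. Without the clustering correction, 80% does not describe even this test at the recruited number.

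**3. The paired version of the same binary comparison.** McNemar test, with d = 0.42, b the proportion of women who go from present to absent, and discordance pd = 0.42 + 2b:

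n = [1.96√pd + 0.842√(pd − d²)]² / d²

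| b | Meaning | n for 80% power |
|---|---|---|
| 0 | nobody loses the taxon | 17 |
| 0.084 | occasions uncorrelated | 24 |
| 0.27 | largest possible discordance | 41 |

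The documents give no discordance, so the requirement is a range, 17 to 41.

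**4. The named paired t-test** (two-sided 0.05, 80% power). Detectable mean change, in SDs of the change: 0.50 at n = 34 and 0.43 at n = 45.

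**5. The between-phase comparison.** Let s² be the variance at one visit and ρ the correlation between visits.

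*As planned (independent-sample t-test).* The nominal detectable difference is 0.69 SD at n = 34 and 0.60 at n = 45. However, the two changes, T1−T0 and T2−T1, come from the same women and share T1. With equally correlated visits each has variance 2s²(1−ρ) and their covariance is −s²(1−ρ), so they correlate at −0.5. The test assumes the difference in means has variance 4s²(1−ρ)/n; it is really 6s²(1−ρ)/n. Type I error is 2[1 − Φ(1.96/√1.5)] = 11%. A simulation at n = 37 also gave 11%.

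*Paired alternative.* Each woman's difference of changes is T2 − 2T1 + T0.
- Equally correlated visits: variance 6s²(1−ρ), so its SD is √3 times that of one phase's change. Detectable difference: 0.495 × √3 = 0.86 SD at n = 34 and 0.427 × √3 = 0.74 SD at n = 45.
- First-order autoregressive decay, with ρ between adjacent visits: variance 2s²(1−ρ)(3−ρ), so the ratio is √(3−ρ). At n = 34 this gives 0.72 SD at ρ = 0.9, rising to 0.86 SD at ρ = 0.

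**The case against.** The section says it sizes a pre-post difference, so pairing was intended, and the design effect only raised N. The Discussion gives reasons for choosing Oscillospira as the marker. Statistical analysis treats sequencing data in a separate sentence, and a test of taxon presence could sit in an analysis plan that is not shown. These points soften the criticism without removing it: the article states both its sizing variable and its tests, and they do not match.

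A reader might go further and infer any of the following. The documents do not support them.

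- **That 45 is too few.** Nothing shows this. On the plan's own rates 45 exceeds the paired binary requirement at every possible discordance. The 34 evaluable fall below it only at high discordance. For the t-tests no target effect is given against which adequacy could be judged.
- **That the source study is described inconsistently.** Sample size takes its rates from a study "on high fiber food-based diet where percentage presence of" Oscillospira was reported, while Background cites the same reference for a fermented-food diet. The Discussion says that study covered both fermented and high-fibre foods. Whether a high-fibre effect suits a fermented-rice trial is a judgement.
- **That 31% and 73% are impossible with 18 people.** This holds only if all 18 gave samples at both visits. With missing samples both are attainable (5/16 = 31%, 11/15 = 73%).
- **That a null result would be uninterpretable.** Confidence intervals can be read whatever formula set N.

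**Conclusion.** The point stands in this form: the stated 80% power applies to no test the protocol names, and the design effect of 2 has no basis in a single-hostel, individually sampled, within-woman design. The mismatch follows from the text and needs no outside figure.

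Its size is best seen in what the trial can detect: half an SD of the change for the pre-post test with 34 women, and roughly 0.7 to 0.9 SD of a single-phase change for a valid between-phase contrast. The latter figures assume equally correlated or autoregressive visits, equal variance across visits and 25% loss. They belong to a paired contrast, not to the independent-sample test now planned. The finding concerns the justification and the match between test and design. It does not concern the number recruited.

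**What to change.** Keep 45 and rewrite the section:

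1. Delete the two-proportion formula and the design effect.
2. State detectable effects at two-sided 0.05 and 80% power. For the paired pre-post t-test: 0.50 SD of the change with 34 evaluable, 0.43 SD with all 45.
3. In Statistical analysis, replace the independent-sample t-test with a paired test of each woman's two changes (T2 − 2T1 + T0). Then state about 0.86 SD of a single-phase change at n = 34 (0.74 at n = 45) under equally correlated visits, with about 0.72 to 0.86 at n = 34 if correlation decays with time.
4. If the 31%/73% presence basis is kept, add a McNemar test of presence and size for it with a stated discordance (17 to 41 women).
5. Correct beta from 0.02 to 0.2.

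The cost is one rewritten section and one changed test, with no extra participants. The downside is a less favourable stated detectable effect for the controlled contrast.

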**Methods:**

This is a single arm, non-randomized controlled trial among 45 women aged 20–35 years, purposively selected from a residential hostel in Colombo District, Sri Lanka. The primary outcomes: gut microbiome composition, nutritional status, and health and immune markers will be assessed before and after a 10-week control phase, during which participants will follow their usual dietary habits (control). In the subsequent 10-week intervention phase, the same participants will consume *diyabath* daily as a pre-breakfast meal (intervention). The *diyabath* will be prepared according to an optimal recipe identified through a comprehensive evaluation of traditional recipes during the intervention development phase. Outcomes will be reassessed immediately and one month after completing the intervention. Changes in outcomes between the control and intervention phases will be compared.

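### The stated 80% power is for presence or absence of one genus in two independent groups, so it applies to none of the t-tests the protocol plans, including the between-phase comparison

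*Protocol article*

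**What the plan says.** **Sample size section.** The target is described as follows: "The study is designed to detect a significant difference in the pre- and post-intervention time points for a given dichotomous variable". N is defined as "Minimum sample size required for each group". The two proportions come from a cited diet study in which presence of *Oscillospira* "at baseline was 31% and at the end of the intervention was 73" per cent. They are assigned to T1 and T2. Alpha is 0.05 and power 0.8. The factor f is given as 7.9, beside a printed beta of 0.02. The result, 18.41, is doubled for a design effect and then raised for non-response to 45.

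**Outcomes section.** The microbiome outcome consists of percentage abundances (*Oscillospira* among them), an alpha-diversity index and the Firmicutes-to-Bacteroidetes ratio. The other primary outcomes are serum and blood concentrations. None is defined as present or absent.

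**Study design and Implementation sections.** One group of women passes through both the control phase and the intervention phase.

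**Statistical analysis section.** "Paired t-test will be performed to determine the significance of the mean difference of pre- and post- measurements during the intervention phase". The same test is applied to the control phase. An independent-samples t-test then compares the mean change in one phase with the mean change in the other. No test of proportions is named.

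**Abstract, Methods.** "Changes in outcomes between the control and intervention phases will be compared".

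**The concern.** A power statement is useful only if it refers to the variable, design and test that will be reported. Here all three differ: a yes/no variable against continuous outcomes, two independent groups against one group measured repeatedly, and a comparison of proportions against t-tests on means. Someone reading the results would naturally attach the 80% to the reported t-tests.

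The between-phase comparison is the more exposed of the two. Without a concurrent control group, it is the analysis that separates an effect of the food from the seasonal, physiological or climatic drift that the Statistical analysis section itself mentions. The sizing covers only T1 to T2, so the article gives no indication of how large a between-phase difference the trial could detect.

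**Working it through.** **1. The plan's own figure.** Inputs from the Sample size section: p1 = 31, p2 = 73, f = 7.9.

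N = {31×69 + 73×27} × 7.9 / (31 − 73)² = (2139 + 1971) × 7.9 / 1764 = 18.41.

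This reproduces the printed value. The numerator adds two binomial variances and has no term for discordance or correlation within a woman, so it is the formula for two independent proportions. Doubling gives 36.82. Multiplying by 1.25 gives 46.03, against the printed 45; that small gap does not affect this point.

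**2. Beta.** For two-sided alpha 0.05, f = (z₀.₉₇₅ + z₁₋β)². Beta 0.2 gives 7.85 and beta 0.02 gives 16.11. The value 7.9 therefore goes with beta 0.2, as does the stated power of 0.8. The printed 0.02 is a misprint and changes no result.

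**3. Paired t-test, T1 to T2.** Two-sided 0.05, 80% power, noncentral t with n − 1 degrees of freedom and noncentrality d√n, where d is the mean change divided by the SD of the change. The values of n are 45 (enrolled), 37 (36.82 rounded up) and 34 (45 × 0.75 = 33.75, rounded up).

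| n | detectable d |
|---|---|
| 34 | 0.50 |
| 37 | 0.47 |
| 45 | 0.43 |

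**4. Between-phase contrast, analysed within woman.** The contrast is (T2 − T1) − (T1 − T0). If the two changes have equal variance and correlate at c, its SD is √{2(1 − c)} times the SD of one change. The documents give no c, so a range is shown. The power column takes the effect that has 80% power in step 3 and assumes no change in the control phase. The power values agree at all three n to the precision shown.

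| Assumption | SD factor | Power | Detectable difference, in SD of one change (n = 37; n = 45) |
|---|---|---|---|
| Equal variances and equal correlations between visits (c = −0.5) | √3 | about 37% | 0.82; 0.74 |
| AR(1), r = 0.5 (c = −0.25) | √2.5 | about 43% | 0.75; 0.68 |
| AR(1), r = 0.7 (c = −0.15) | √2.3 | about 46% | 0.72; 0.65 |
| Changes uncorrelated (c = 0) | √2 | about 51% | 0.67; 0.60 |
| Changes correlate +0.25 | √1.5 | about 63% | 0.58; 0.52 |

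For AR(1) the variance ratio is 3 − r, because Var(T2 − 2T1 + T0) = 2s²(1 − r)(3 − r) and Var(T2 − T1) = 2s²(1 − r).

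**5. The planned independent-samples t-test.** It treats the two sets of changes as if they came from different women. Both come from the same women and share T1, which enters one change with a plus sign and the other with a minus sign. Under equal variances and equal correlations r, the true variance of the contrast is 6s²(1 − r), while the test assumes 4s²(1 − r). The nominal cut-off of 1.96 then acts as 1.96/√1.5 = 1.60, a two-sided error of about 0.11. Simulation at r = 0.3 and 0.7 with 37 and 45 women gave 0.108 to 0.115; a paired test gave 0.049 to 0.053.

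**The case against.** The sizing variable is not foreign to the trial. *Oscillospira* is a named part of the microbiome outcome, the Discussion defends its presence as a marker of gut health, and T1 to T2 is the interval that the Statistical analysis section uses to determine the effect of the food. The between-phase test is introduced there as a further analysis. An analysis plan that is not shown might add a test of proportions. All of this is fair. It narrows the mismatch to scale, design and test but does not remove it: even with an added test of proportions, the t-tests named in the article would have no stated power.

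Four stronger readings are tempting and are not supported.

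- *The trial is underpowered.* No SD, expected change or correlation is given for any continuous outcome, so the power of the t-tests is unknown, not low.
- *The planned between-phase test has 37% power.* That figure is for a within-woman test, which the protocol does not plan, under one correlation structure. At the same effect and under that structure, the planned independent-samples test rejects about 52% of the time, but with a type I error of about 0.11, so that is not usable power.
- *The sizing comparison really has well over 80% power because 37 women exceed 18.41.* The protocol attaches 80% to 18.41 and doubles it for an assumed design effect of 2. Whether that factor belongs here is a separate question.
- *31% and 73% cannot arise from 18 participants.* This depends on how many samples were available at each visit in the cited study, which the documents do not say.

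**Conclusion.** The point holds in a limited form: the 80% applies to no analysis named in the article, neither the paired t-tests nor the between-phase comparison. That conclusion follows from the text and the reproduced 18.41, and needs no outside assumption.

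The size of the consequence does rest on assumptions. The T1–T2 detectable changes need only approximate normality of the change. The 37% to 63% range for the between-phase contrast depends on correlations that the documents do not supply, and nothing in them favours one row of the table over another. The inflated error of the planned independent-samples test is likewise conditional on equal variances and equal correlations; it would vanish if the two changes happened to be uncorrelated. The beta misprint is minor.

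**What to change.** Keep enrolment at 45 and rewrite the Sample size section:

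1. State the detectable standardised change for the T1–T2 paired t-test at 34, 37 and 45 women.
2. State the detectable difference for the between-phase contrast over the range of correlations tabulated above. Analyse that contrast within woman (a paired t-test of the two changes), and say openly that this replaces the planned independent-samples t-test.
3. If presence of *Oscillospira* remains the sizing variable, list it as an outcome and name McNemar's test for it. Otherwise remove the dichotomous calculation as the basis for the power claim.
4. Correct beta from 0.02 to 0.2.

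The cost is a rewritten paragraph and one changed test, with no extra participants or measurements. The drawback is that the stated sensitivity of the between-phase comparison will look less favourable than the present text suggests.

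### The 31% and 73% behind the sample size do not fit the 18 adults they are attributed to, and the 80% power is for a yes/no variable the trial does not analyse

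*Protocol article*

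**What the plan says.** The Sample size section says the study is designed "to detect a significant difference in the pre- and post-intervention time points for a given dichotomous variable". Its formula is N = {p1(100 − p1) + p2(100 − p2)} × f / (p1 − p2)², with f = 7.9 for a 5% significance level and 80% power.

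The inputs are P1 = 31% at T1 and P2 = 73% at T2. Both are taken from a "17-week randomized controlled intervention study (*n* = 18, healthy adults) on high fiber food-based diet", in which the *percentage presence* of *Oscillospira* "at baseline was 31% and at the end of the intervention was 73" per cent. The justification offered is: "Previous studies have used the percentage presence of selected taxonomic groups of microbiota to interpret the gut microbiome changes". The unit being counted (participants, samples or sequence reads) is not given, and neither is the number of adults contributing at each time.

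The result, 18.41, is doubled for a design effect to 36.82 and raised for 25% non-response to a final 45.

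The Outcomes section describes gut microbiome composition differently: "Evaluated using percentage abundance of probiotic strains" and of other beneficial organisms, *Oscillospira* among them. The Statistical analysis section says: "Paired t-test will be performed to determine the significance of the mean difference of pre- and post- measurements during the intervention phase". It adds a second t-test comparing the mean changes of the two phases, and names no test for a yes/no variable.

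**The concern.** A formula with variance p(100 − p) needs each percentage to be a share of participants who are positive on a yes/no variable. A share of 18 people moves in steps of 5.6 points, so whether 31% and 73% can be such shares is easy to check. They are the only empirical inputs to 18.41, 36.82 and 45. If they are not shares of participants, the formula does not apply to them.

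The second question is whether the stated power describes the analysis that will be run. Power to detect a rise in the share of women carrying a genus is not power to detect a mean change in its relative abundance. The latter depends on the standard deviation of the within-woman change, which does not enter the calculation.

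**Working it through.** **1. The plan's own figure.** From the Sample size section: p1 = 31, p2 = 73, f = 7.9.

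- Variance term: 31 × 69 + 73 × 27 = 2139 + 1971 = 4110.
- Squared difference: 42² = 1764.
- N = 4110 × 7.9 / 1764 = 18.41, as stated. Doubled: 36.82, as stated.

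The arithmetic from the inputs is correct. The question is the inputs.

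**2. Can they be counts out of 18?** 18 × 0.31 = 5.58 and 18 × 0.73 = 13.14, neither a whole number. The neighbours are:

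- near 31%: 5/18 = 27.8% and 6/18 = 33.3%
- near 73%: 13/18 = 72.2% and 14/18 = 77.8%

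None rounds to the printed figure.

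**3. Can they share a smaller denominator, if samples were missing?** Up to 18, 31% arises only as 4/13 or 5/16, and 73% only as 8/11 or 11/15. The smallest denominator that gives both is 26 (8/26 = 30.8%, 19/26 = 73.1%).

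**4. How much could it matter?** The plan's formula with the nearest eighteenths gives the table below. The final column applies the 25% as × 1.25 and as ÷ 0.75, because the text does not say which is meant. The power column uses the normal approximation that matches the formula, Φ(√(18.41 (p1 − p2)² / variance term) − 1.96). It is evaluated at 18.41, which is 36.82 divided by the design effect of 2.

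| Pair | N | × 2 | With 25% allowance | Power at 36.82 |
|---|---|---|---|---|
| 6/18 to 13/18 | 22.1 | 44.2 | 55.2 to 58.9 | 73% |
| 5/18 to 13/18 | 16.0 | 32.1 | 40.1 to 42.8 | 85% |
| 6/18 to 14/18 | 15.8 | 31.6 | 39.5 to 42.1 | 86% |
| 5/18 to 14/18 | 11.8 | 23.6 | 29.5 to 31.5 | 94% |

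First row as an example: variance term 4228.4, squared difference 1512.3, so N = 4228.4 × 7.9 / 1512.3 = 22.1, and √(18.41 × 1512.3 / 4228.4) − 1.96 = 0.61, giving Φ = 0.73.

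If the source had 16 adults with samples at baseline and 15 at the end, 5/16 and 11/15 give N = 18.3, practically the plan's own figure.

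**5. Formula against analysis.** The Sample size section assumes a yes/no variable. The Outcomes section defines a percentage on a continuous scale, and the Statistical analysis section tests means. For a paired t-test the smallest standardised mean change (mean change divided by the SD of the change) detectable with 80% power is about √(f / n):

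- 45 women: √(7.9 / 45) = 0.42
- after 25% loss, 45 × 0.75 = 33.75: √(7.9 / 33.75) = 0.48

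These use no design effect. Keeping the plan's factor of 2 multiplies each by √2, to 0.59 and 0.68. The documents give no SD of change, so these cannot be turned into percentage points of abundance.

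**The case against.** The strongest defence is that P1 and P2 are labelled as expected percentages derived from a study. A planning value need not be an attainable fraction of the sample it came from. Nor does the two-proportion formula need a common denominator or matched adults: it uses two separate percentages, so 5/16 and 11/15 would be valid inputs and would leave 18.41 almost unchanged. This stands. It rules out a reading that a reader might infer from the integer check, namely that the two figures are shown not to be proportions and that the size of 45 has no basis. The documents do not support that. The check excludes 18 as the denominator of either figure; it does not say what the true denominator or unit was.

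The range of sizes also needs care. It combines the neighbours on both sides of each figure, 18.41 lies inside it, and three of the four pairs need fewer women than planned. The one pair below 80% falls there only because the design effect of 2 is kept.

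The protocol's Discussion can be cited both ways. It treats detection of *Oscillospira* as the marker, which favours a yes/no reading. It also describes the genus as one that 16S surveys regularly find, which sits awkwardly with presence in 31% of adults, and it argues from correlations with its abundance. This does not settle the unit.

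None of this answers the mismatch between a formula for a yes/no variable and an analysis of means.

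**Conclusion.** Two things are established from the protocol alone.

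- **The inputs do not fit their stated source.** Neither 31% nor 73% is a count out of 18, and no denominator below 26 gives both. Different denominators at the two times, another group, or a unit other than participants would each explain this. Choosing between them needs the cited study.
- **The 80% power is not that of the planned analysis.** It belongs to a comparison of two proportions, whereas the outcome is percentage abundance and the tests compare means.

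It is not established that 45 is too small. On the assumption that the true values are the nearest eighteenths, the base figure lies between 11.8 and 22.1 and the final size between about 30 and 59. Power at the plan's 36.82 is then about 73% for the least favourable pair and 85% to 94% for the others. The point deserves correction because these two percentages are the whole empirical basis of the sample size, but it does not call for a larger trial.

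**What to change.** In the Sample size section:

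1. Return to the cited study and give P1 and P2 as counts over denominators at each time, naming the group and the unit counted. If they are shares of participants, recompute 18.41 and 36.82 from those counts. If they are relative abundances or another unit, drop the two-proportion calculation.
2. In either case keep 45 and restate the power for the paired mean change from T1 to T2 in the outcome as it is measured, with the assumed SD of the change and its source. If no SD is available, state the smallest detectable standardised change. By the normal approximation and without a design effect this is about 0.42 with all 45 women and 0.48 after 25% loss.

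The cost is rereading one source and rewriting one paragraph. The restated power may look less favourable. No participants or visits are added.
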